#### Identifying and building a model for predictive and prescriptive factors

Using the Personalised Advantage Index (PAI) approach, we will investigate which form of therapy works optimally for subgroups of depressed patients [27]. The aim is to build and validate a predictive model using machine learning techniques that combines multiple predictors and moderators to make predictions regarding the optimal, expected effectiveness of treatment for a specific patient on the basis of the interaction between patient characteristics and the type of treatment [24]. If the PAI actually has predictive value, it can be expected that patients who by chance receive the treatment method that does not match the PAI score in phase one are the ones that will benefit most from a switch of treatment method. Exact statistical procedures regarding PAI development are beyond the scope of this study protocol and they will be discussed in the relevant publications.

#### The effect of therapist or therapy change after initial non-response

The effect of different follow-up treatment strategies, after an initial non-response to treatment (defined as an improvement of less than 50% over the initial measurement on the IDS-SR), on depressive symptoms, functional impairment and positive mental health will be analysed using multilevel repeated-measures linear-mixed modelling with group, time and group × time interaction as fixed factors.

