### Power and sample size calculation

To calculate the required sample size for the first phase of the study we used the original dataset provided by the authors of a similar study which was conducted in a similar setting and population [19]. We expected this to be the best data available to make an accurate estimate of the standard deviation of the primary outcome needed to calculate the sample size.

The primary outcome measure of the current study is the severity of depressive symptoms as measured by the IDS-SR [52]. To test whether SPSP is in fact (as hypothesised) not inferior to CBT, a treatment that has already proven to be effective for treating MDD, we used the same non-inferiority margin (the maximum allowed difference in the mean outcome scores between the treatment groups to conclude that SPSP is indeed non-inferior to CBT) for continuous measures as Driessen et al. [19, 53] Accordingly, we adopted a non-inferiority margin of five points on the mean score on the IDS-SR immediately after treatment. This margin of a five-point difference between SPSP and CBT corresponds to a Cohen’s d of .30, which we assume to be a clinically acceptable difference. Power analysis for continuous outcomes [54] indicated that, to prove that SPSP is not inferior to CBT, 268 patients in total are needed for the first part of the study to provide 80% power in order to demonstrate that the lower limit of the one-sided 95% confidence interval (CI) will be above the non-inferiority limit of − 5 for the IDS-SR (1-β = 80%, SD = 16.42). Given the observed dropout rate of around 15% for the first 100 included patients, the aim is to include 308 patients for the performance of the per-protocol analysis.

Assuming that approximately 52% of the patients will be classified as non-responder after the first phase of study [4], we estimate that around 139 patients can be randomized across the three groups (1. same therapist, same treatment, 2. a switch of therapist only, 3. a switch of therapist and treatment) in the second phase of the study. According to a sensitivity analysis, by means of an analysis of covariance (ANCOVA), this suggests that we can significantly (α = .05) demonstrate a medium to large effect size (f = 0.35) with 80% power between the three groups in the second phase of the study.

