### Randomisation

We use two potential moderators of outcome: severity (IDS-SR score < 39 or ≥ 39) and duration of depression (longer or shorter than 2 years) as stratification variables. Randomisation takes place using a system with closed envelopes in which the researcher is kept blinded to treatment allocation until the completion of the study phase and the patient is blind to the research condition until the start of the therapy. The therapist is given the information about the type of treatment to be administered shortly before the start of therapy.

Randomisation lists with an 1:1 allocation ratio were drawn up prior to the start of the inclusion of patients using an online tool [58]. Random block sizes are used. Block randomisation for phase two follows the same procedure as phase one, with an allocation ratio of 1:1:1. Patients receive a unique randomisation code that is linked to a unique patient number in the data file. The coding key is known to only one independent person. That person manages the data file that will be used for statistical analysis.

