### Statistical analysis

#### Establishing non-inferiority

The study compares the effectiveness of two forms of treatment (SPSP and CBT). The primary dependent variable is the average post-treatment score for the two groups on the IDS-SR. An ANCOVA with treatment type received as a fixed effect and baseline depression scores measured on the IDS-SR as a covariate will be performed to calculate the mean and 95% CI of the difference between the groups at the final time point on the IDS-SR. This analysis forms the basis for demonstrating that SPSP reduces depressive symptoms at least as effectively as CBT. If the lower limit of the 95% CI is above the non-inferiority limit of − 5 on the IDS-SR, it will be assumed that SPSP is not inferior to CBT. Non-inferiority analysis will be performed on the basis of both per protocol and intention-to-treat analysis.

Additional multilevel repeated measures will be used to further analyse changes in depressive symptoms and the other secondary outcome measures (functional impairment and positive mental health) and to examine possible differences between both treatment groups over time. If there are significant differences between groups in medication use or other potentially confounding variables, these variables will be included as covariates.

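### The phase-two model does not state that it conditions on the end-of-phase-one score, which costs precision where power is shortest; adding duration to the primary ANCOVA is a minor, free improvement

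*Protocol article*

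**What the plan says.** All references are to the protocol article.

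- **Randomisation.** The stratification factors are introduced as "We use two potential moderators of outcome: severity" (IDS-SR cut at 39) "and duration of depression (longer or shorter than 2 years) as stratification variables". For the second phase, "Block randomisation for phase two follows the same procedure as phase one", at 1:1:1. The method received in phase one is not named as a stratum.
- **Establishing non-inferiority.** The primary model is "An ANCOVA with treatment type received as a fixed effect and baseline depression scores measured on the IDS-SR as a covariate". Further covariates enter only where the groups differ significantly on medication use or another possible confounder.
- **The effect of therapist or therapy change after initial non-response.** Depressive symptoms, functional impairment and positive mental health are to be analysed by "multilevel repeated-measures linear-mixed modelling with group, time and group × time interaction as fixed factors". The text does not say whether or how the score at the end of phase one is used.
- **Power and sample size calculation.** The detectable effect for phase two is introduced with "According to a sensitivity analysis, by means of an analysis of covariance (ANCOVA"; the covariate is not named.
- **Procedures.** Response is judged from the post-treatment IDS-SR against baseline, so the end-of-phase-one score exists for every patient classified in this way as a non-responder.
- **Table 1.** In phase two the IDS-SR is taken at weeks 1, 2, 4 and 8; the SDS and MHC-SF are taken at week 8 only.

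**The concern.** The phase-two power statement and the phase-two model do not describe the same analysis: one is an ANCOVA, the other has no covariate. The stated model can be read in two ways. Either the end-of-phase-one score is left out and the series starts at week 1 of phase two, or it enters as a time-0 outcome with a freely estimated mean in each group. For the SDS and MHC-SF only the second reading works, because a group by time term cannot be estimated from a single phase-two visit. Both readings make poorer use of the starting score than conditioning on it. This concerns the third major objective, in a phase whose limited power the Discussion concedes.

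Two smaller omissions go with it. Each phase-two arm contains patients who began with SPSP and patients who began with CBT, and the model has no term for that. The primary ANCOVA leaves out duration, by which patients are stratified. The rule for adding covariates would rarely admit duration, since stratified blocks keep it balanced.

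**Working it through.** **Inputs from the Power and sample size calculation section.** SD 16.42, margin 5, one-sided 95% limit, 80% power, 268 evaluable patients, 52% non-response, about 139 patients in phase two.

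**Assumptions (the documents give no figures).** Correlation r between the end-of-phase-one and phase-two week-8 scores of 0.4 to 0.7; SD 16.42 at both times and among non-responders; equal groups; complete data; time as a categorical factor; two-sided 5% tests.

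**1. The plan's own figures.** Per arm, 2 × (1.645 + 0.842)² × 16.42² / 5² = 133.4, so 134, or 268 in total: reproduced. Then 0.52 × 268 = 139.4, or 46.3 per group. The stated f = 0.35 does not reproduce: a three-group F test with 139 patients has 80% power at f = 0.266, and f = 0.35 would give 96%. That is a separate matter; the comparison below is in IDS-SR points and does not use f.

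**2. Smallest detectable week-8 difference between two phase-two groups.** The multiplier is 1.960 + 0.842 = 2.802.

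- A, week-8 scores only: SE = 16.42 × √(2/46.3) = 3.41, and 2.802 × 3.41 = 9.6 points.
- B, end-of-phase-one score as unconstrained time-0 outcome: SE = 3.41 × √(2(1 − r)).
- C, conditioned on that score (covariate, or group means constrained equal at that point): SE = 3.41 × √(1 − r²).

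| r | A | B | C |
|---|---|---|---|
| 0.4 | 9.6 | 10.5 | 8.8 |
| 0.5 | 9.6 | 9.6 | 8.3 |
| 0.6 | 9.6 | 8.6 | 7.7 |
| 0.7 | 9.6 | 7.4 | 6.8 |

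The variance ratio of B to C is 2(1 − r)/(1 − r²) = 2/(1 + r), which is 1.33 at r = 0.5 and 1.18 at r = 0.7. That of A to C is 1/(1 − r²), which is 1.33 and 1.96. The ordering does not depend on the assumed r. A subtracts none of the starting score, B subtracts all of it, and C estimates the fraction that leaves the least residual variance.

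**3. Phase-one method.** If half of each group began with each method and allocation is not stratified by it, the between-group difference in the share who began with CBT has SD √(2 × 0.25/46) = 0.104, about 10 percentage points. With an assumed method effect of 5 points, one SD of imbalance moves a contrast by 0.104 × 5 = 0.5 points. Removing that from the SE of C at r = 0.5 (3.41 × 0.866 = 2.96) gives √(2.96² − 0.52²) = 2.91, a gain of less than 2%.

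**4. Duration in the primary ANCOVA.** Simulation of 268 patients, with blocks of 4 within the four severity-by-duration strata, 35% with long duration, baseline IDS-SR in both models (assumed coefficient equivalent to a correlation of 0.4), and the true difference set at the margin; 6,000 runs per row.

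| Duration effect (points) | Model SE without / with duration | One-sided error without / with |
|---|---|---|
| 0 | 1.838 / 1.838 | 4.9% / 4.9% |
| 3 | 1.847 / 1.839 | 5.3% / 5.3% |
| 5 | 1.859 / 1.836 | 5.4% / 5.5% |
| 8 | 1.896 / 1.838 | 4.2% / 4.6% |

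The simulation standard error of a 5% rate is √(0.05 × 0.95/6000) = 0.3 percentage points. Leaving duration out shows no inflation beyond that and is slightly conservative at 8 points, where the model SE is 1.896/1.838 = 1.03 times the adjusted one. The estimates themselves vary equally in both models (SD 1.837 and 1.835 at 8 points).

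**The case against.** The strongest reply is that a condensed article may leave time coding and the handling of starting scores to the SAP, and that the ANCOVA in the power section suggests a covariate was in mind. Part of this stands: the SAP may settle the matter. But the article does list the fixed factors of the phase-two model, and that list does not match its own power section. The mismatch is on the page.

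It is also fair to say that the 2/(1 + r) penalty applies only under the time-0 reading, which the article does not state, and that under this reading the starting score is already used in part. Both points stand, so the loss has to be given for each reading. Conditioning is better under both.

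Three stronger inferences are tempting and are not supported.

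- A reader might infer that leaving out duration makes the non-inferiority interval invalid. It does not: there is no bias and no inflation of error, and severity is already represented by continuous baseline IDS-SR. Even the small overstatement of the SE requires duration to predict outcome given baseline IDS-SR; the article calls it only a potential moderator.
- A reader might infer that mixing SPSP and CBT starters biases the switch group. All three arms are mixed in this way and patients are randomised, so any imbalance is chance.
- A reader might expect a main effect for phase-one method to show whether switching works equally in both directions. That needs an interaction, for which this phase is too small to be more than supportive.

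**Conclusion.** The point holds for phase two, as a loss of precision and an inconsistency between two sections, not as a bias. At an assumed r = 0.5, conditioning lowers the smallest detectable week-8 difference from 9.6 to 8.3 points under either reading. Over r = 0.4 to 0.7 the gain is 0.8 to 2.7 points against week-8 scores only (9.56 − 8.76 and 9.56 − 6.83), and 1.7 to 0.6 points against an unconstrained time-0 outcome (10.47 − 8.76 and 7.41 − 6.83). The sizes rest on the assumed correlations and on carrying the phase-one SD over to non-responders; the direction does not.

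Adjustment for phase-one method is a small precision gain. That phase two uses the severity and duration strata is implied by the reference to the same procedure, not spelled out. In the primary ANCOVA, adding duration is optional good practice: the cost of leaving it out is a standard error overstated by about 0 to 3% for assumed effects of 0 to 8 points. No conclusion that the plan could reach is invalidated.

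**What to change.** In the phase-two model:

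- include the end-of-phase-one score of each outcome as a covariate, or keep it in the outcome series with group means constrained equal at that point;
- add phase-one method and the stratification factors actually used in phase two;
- name the week-8 group contrast as the estimate, and report a group by phase-one-method term as supportive only;
- make the power section and the analysis section describe the same model.

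In the primary ANCOVA, add duration (longer or shorter than 2 years).

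All these variables are already collected. The change is wording in the SAP, or in an amendment before analysis. The degrees of freedom are negligible: with 139 patients, four extra terms move the detectable f at 80% power only from 0.2662 to 0.2663, before counting any gain from adjustment.

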#### Moderator and mediator analysis

Most moderator and mediation analysis regarding allegiance and adherence will be performed with regression-based methods [98]. Additionally, cross-lagged panel analysis will be used to investigate the directionality and reciprocity of the relations between working alliance (WAI) and symptoms (IDS-SR) over time [99, 100]. We will also study whether a cut-off score for the working alliance can be determined that is predictive of a significantly lower treatment result by means of an receiver operating characteristic analysis. In line with Zilcha-Mano [101] the relative speed of change in the quality of the working alliance for each patient will also be explored in an additional analysis as a possible factor that influences outcome since, in her theory, some patients are better equipped to benefit from the therapeutic relationship.

## Discussion

The overarching purpose of the study described in this protocol is to acquire knowledge that can help increase the effectiveness of psychotherapy for depression in clinical practice. We aim to do this by addressing a number of research questions in one study with a comprehensive design. Some of these questions have never been the direct focus of a research project. By enrolling depressed outpatients who are randomised to two active treatment conditions (CBT and SPSP), we start the study with a non-inferiority design. This design enables us to address multiple issues. We are able to explore whether SPSP is non inferior to CBT, which extends the evidence base of psychodynamic psychotherapy for depression, which is frequently applied but still relatively understudied. We hope the study will also reveal prescriptive and prognostic factors for treatment response. We will try to build and validate a model which enables us to predict which treatment works best for whom, in other words to personalise treatment. Developing personalised treatment selection strategies is a very promising way to increase the effectiveness of psychotherapy. In the D*Phase study, prediction based on PAI in the first phase of the study can be validated on the basis of the treatment results in phase two of the study.

A novel aspect of the design is found in the second part of the study, which focuses on patients who do not benefit (or who do not benefit enough) from psychotherapy. This is often the case in clinical practice. These patients are randomised again into three groups (continuing the initial treatment with the same therapist, continuing the initial treatment with another therapist and continuing the other type of treatment with another therapist). This provides us with opportunities to find evidence for the expert-based advice given in practice guidelines for the treatment of MDD. The guidelines tell us to switch to another kind of therapy when not enough progress is made but there is no empirical evidence for this advice. Furthermore, we explore what happens when patients switch to another therapist. This is particularly interesting given the assumption made by some researchers that the effects of psychotherapy largely depend on common factors.

By incorporating questionnaires on the working alliance and therapist characteristics that are completed at different points in time, we hope to gain insight into the influence of the working alliance on the effect of psychotherapy. The repeated measures design will provide an opportunity to evaluate whether symptom change occurs in advance of, and is related to, the working alliance. This is one of only a few studies this temporal effect. We also hope to shed light on whether, and which, characteristics of the therapist have an effect on the working alliance and we will address the topic of the relevance of therapist allegiance, with the treatment methods studied, as a predictor of treatment outcome.

The current study is distinctive in the sense that it provides an opportunity to explore the influence of an important common factor (the alliance) and also therapy-specific factors (treatment differences and treatment integrity) on treatment effect in a single, large cohort. Treatment integrity is adequately measured for both conditions. The study also provides several openings for post-hoc analysis. For example, if we find that the therapy and/or therapist switch has an effect, we will be in a position to determine which factors contribute to a possible effect of the switch. If there should indeed be a relationship between competence/adherence and treatment effect, this could be a cautious indication that method-specific interventions *do* matter in psychotherapy. Of course, findings will only remain global indications and there is no way to measure all possible factors that could play a role.

We therefore intend to implement a pragmatic, methodically strong, study in which the naturalistic setting will contribute to the generalisability of the results to everyday practice. This is a challenging undertaking and it also has certain limitations. Due to the naturalistic setting, for instance, it is not possible to control completely for the use of medication, although the use of medication is monitored and, if necessary, statistically controlled for in the analysis. Different treatment options for depression are available in the treatment centres and patients can choose a different kind of treatment offered by the treatment centre and refused to participate in the research project. This may result in a bias. Secondly, a double-blind design is never possible in a psychotherapy study because the therapist and patient are obviously aware of the kind of treatment that is being administered. However, by digitalising the administration of all the questionnaires that are used, both researchers and therapists are blinded to all patient-reported results and researchers are blinded to the treatment conditions. Thirdly, in spite of the fact that we include several potential predictors, one possible mediator and several moderators, there will certainly be important factors (latent and otherwise) that are not assessed in the current study. Lastly, because the study is primarily powered for the non-inferiority phase, it is expected that phase two of the study only has sufficient power to detect medium to large differences between the groups. Despite this relatively limited power, we still expect this phase of the study will generate meaningful observations on the effects of therapist and treatment switching.

The therapists in the study are thoroughly trained and supervised in the treatment methods concerned in order to ensure that the non-inferiority part of the study will not be biased too much by differences in therapist competence with respect to the different treatment methods. However, most therapists are expected to have more experience with CBT. We will be able to take treatment experience into account as a confounder in our statistical analyses. Furthermore, the measurement of treatment allegiance and treatment integrity will allow for statistical correction for confounding by these factors, at least when it proves to be relevant to do so. There is no instrument to measure treatment integrity for SPSP and so it has to be developed during the course of the study.

Despite these limitations, the design of this study, which compares two different treatments head-to-head, means it will have implications at different levels. In addition to enhancing the evidence base for SPSP, it can teach us more about prescriptive factors for different treatments for MDD and shed light on the role of the therapist in terms of maximising treatment effect by studying the working alliance and the effect of treatment integrity and allegiance. On top of that, this study is the first to manipulate the therapist as a factor through a switch of psychotherapist when therapy does not have the intended effect on depressive symptoms. In conclusion, we hope to provide a large number of new insights that will help to increase the effectiveness of psychotherapy and contribute to the improvement of health care for adults suffering from MDD.

## Data Availability

The datasets used and/or analysed during the current study are available from the corresponding author on reasonable request.

